## Abstract

**Background:**

Aseptic loosening of total hip arthroplasties is generally caused by periprosthetic bone resorption due to tissue reactions on polyethylene wear particles. *In vitro* testing of polyethylene cups incorporated with vitamin E shows increased wear resistance. The objective of this study is to compare vitamin E-stabilized highly cross-linked polyethylene with conventional cross-linked polyethylene in “reversed hybrid” total hip arthroplasties (cemented all-polyethylene cups combined with uncemented femoral stems). We hypothesize that the adjunction of vitamin E leads to a decrease in polyethylene wear in the long-term. We also expect changes in bone mineral density, less osteolysis, equal functional scores and increased implant survival in polyethylene cemented cups incorporated with vitamin E in the long-term.

**Design:**

A double-blinded randomized controlled trial will be conducted. Patients to be included are aged under 70, suffer from non-inflammatory degenerative joint disease of the hip and are scheduled for a primary total hip arthroplasty. The study group will receive a reversed hybrid total hip arthroplasty with a vitamin E-stabilized highly cross-linked polyethylene cemented cup. The control group will receive a reversed hybrid total hip arthroplasty with a conventional cross-linked polyethylene cemented cup. Radiological follow-up will be assessed at 6 weeks and at 1, 3, 5, 7 and 10 years postoperatively, to determine polyethylene wear and osteolysis. Patient-reported functional status (HOOS), physician-reported functional status (Harris Hip Score) and patients’ physical activity behavior (SQUASH) will also be assessed at these intervals. Acetabular bone mineral density will be assessed by dual energy X-ray absorptiometry (DEXA) at 6 weeks and at 1 year and 2 years postoperatively. Implant survival will be determined at 10 years postoperatively.

**Discussion:**

*In vitro* results of vitamin E-stabilized polyethylene are promising, showing increased wear resistance. However, controlled clinical follow-up data are not available at this moment.

This randomized controlled trial has been designed to determine wear, bone mineral density, functional outcome and survival in reversed hybrid total hip arthroplasty comparing cemented vitamin E-stabilized highly cross-linked polyethylene cups with cemented conventional cross-linked polyethylene cups.

**Trial registration:**

Dutch Trial Registry NTR3049

## Background

The most important factor for late implant failure in total hip arthroplasty is aseptic mechanical loosening of one or both components. The Nordic arthroplasty registries (Sweden, Norway and Denmark) show aseptic loosening as the main reason for revision in total hip arthroplasty (34.8-50.4%), followed by dislocation (23.4-33.5%) and infection (15.0-15.8%)
[1]. Periprosthetic bone resorption, due to a cellular- and molecular-mediated foreign body reaction to polyethylene wear particles, is one of the main causes for this loosening
[2,3].

In the 1950s and 1960s, total hip arthroplasty was performed using a metal-on-metal articulation
[4,5]. In the 1970s, due to the success of Charnley’s low friction arthroplasty
[6], metal-on-polyethylene articulations were increasingly applied. As polyethylene wear particles turned out to promote aseptic loosening, newer polyethylenes were developed to reduce wear. In the 1990s first-generation cross-linked ultra high molecular weight polyethylenes were introduced. This development led to a reduction in polyethylene wear. In looking for alternative bearing couples lacking the issue of polyethylene wear, the use of hard-on-hard bearings like metal-on-metal and ceramic-on-ceramic increased, especially in young active patients
[7].

Hard-on-hard bearings also have shown disadvantages though. Although rare, ceramic articulations might lead to fracture of the ceramic bearing and produce squeaking noises
[8]. Concerns remain over metal-on-metal articulations because of the metal ion release and subsequent elevated serum metal ion concentration
[9]. Moreover, unpredictable local tissue reaction on metal particles can result in pseudo-tumor formation around the hip joint and perivascular lymphocytic infiltration because of a delayed-type hypersensitivity reaction (aseptic lymphocytic vasculitis associated lesion, ALVAL)
[10]. A metal-on-polyethylene articulation seems therefore to be advocated above metal–on-metal articulation in total hip arthroplasty
[11].

Wear characteristics of ultra-high molecular-weight polyethylene have been improved by the cross-linking technique
[12,13]. A disadvantage is the increased oxidation and decreased fatigue strength of the polyethylene due to the irradiation, remelting and annealing process used in this technique. To prevent oxidation and increase mechanical strength, second-generation highly cross-linked polyethylene has been developed by incorporating vitamin E
[14,15]. *In vitro* testing of these vitamin-E stabilized polyethylene cups shows good wear properties and improved mechanical and fatigue properties
[16]. The influence of vitamin E-stabilized polyethylene cups on acetabular bone mineral density (BMD) is unknown. Hypothetically, this modified polyethylene leads to changes in acetabular bone mineral density due to its different mechanical properties.

The objective of this study is to compare vitamin E-stabilized highly cross-linked polyethylene with conventional cross-linked polyethylene in “reversed hybrid” total hip arthroplasties (cemented all-polyethylene cups combined with uncemented femoral stems). We hypothesize that the adjunction of vitamin E to polyethylene leads to a decrease in polyethylene wear in the long-term (primary outcome parameter). We also expect changes in BMD, less osteolysis, equal functional scores and increased implant survival in polyethylene incorporated with vitamin E (secondary outcome parameters) in the long term. The present paper reports on the design of the study.

## Methods

### Design

A randomized controlled trial will be conducted. Patients are randomized into one of the two treatment groups using concealed envelopes. Cluster randomization (per 10 patients) will be applied and the random allocator sequence will be computer-generated by an independent planner. Envelopes are opened one week before surgery. Patients are blinded for treatment. Only the surgeon and the primary investigator are aware of the allocation type. Follow-up is therefore done by an independent investigator, who is blinded for the treatment allocation. The study design, procedures and informed consent are approved by the local Medical Ethical Committee (registration number 2011-29). The trial is registered in the Netherlands Trial Registry (NTR3049). Guidelines of the Consort Statement are followed
[17].

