### Sample size

It is our hypothesis that reversed hybrid total hip arthroplasties with vitamin E-stabilized polyethylene will show less polyethylene wear at 10 years compared to reversed hybrid total hip arthroplasty without the adjunction of vitamin E. In order to detect at least a clinically relevant difference in wear of 0.5 mm with a standard deviation of 0.07 mm, 63 patients are needed in each group (alpha 0.05, power 0.80). Based on previous studies we expect a drop-out rate of 15%. We therefore aim to include 75 patients in each group, thus 150 patients in total.

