#### Univariate analysis

Student’s *T*-test will be used to determine if there is a difference in wear at 10 years postoperatively between the two groups. Differences in other outcome measures (osteolytic changes, bone mineral density, HOOS, Harris Hip score, SQUASH) between the two groups will also be analyzed with a student’s *T*-test (or non-parametric equivalent in case of a skewed distribution) at different measurement points.

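### The plan names cluster randomization per 10 patients, which contradicts its own patient-level allocation, sample size and analysis; permuted blocks were most likely meant

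*Protocol article*

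**What the plan says.** The Design section of the protocol article first describes allocation of single patients: "Patients are randomized into one of the two treatment groups using concealed envelopes". The next sentence names a different method: "Cluster randomization (per 10 patients) will be applied and the random allocator sequence will be computer-generated by an independent planner". It does not define a cluster or say whether the ten patients of a set share one cup. The section adds: "Envelopes are opened one week before surgery". On blinding of staff it says: "Only the surgeon and the primary investigator are aware of the allocation type". According to Study population, the trial runs in one department.

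The Sample size section gives 63 evaluable patients per group ("alpha 0.05, power 0.80") and a 15% drop-out allowance, and concludes: "We therefore aim to include 75 patients in each group, thus 150 patients in total". It mentions no intracluster correlation (ICC) and no design effect. Under Univariate analysis, the primary comparison is a Student's t-test that "will be used to determine if there is a difference in wear at 10 years postoperatively between the two groups". The GEE under Multivariate analysis models change over time with covariates and does not mention sets of ten.

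**The concern.** The unit of randomization decides which sample size and which test are valid. If sets of ten are allocated together, there are 15 randomized units instead of 150. Patients in one set may then be alike through calendar period, surgeon or learning, and a patient-level test ignores this. Once the first envelope of a set is opened, the rest of the set is also known to anyone who knows its limits. If sets of ten are balanced blocks, none of this applies, and the only issue is how predictable the end of each block is.

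As printed, the text does not tell a reader which design will be run. Someone who generated the list from that sentence could produce a design that the rest of the plan does not fit, and this could not be repaired after enrolment.

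**Working it through.** **Step 1: the plan's own sample size.** The formula for two means is n per group = 2(1.96 + 0.842)² / d², where d is the difference divided by the SD.
- With the printed inputs ("clinically relevant difference in wear of 0.5 mm with a standard deviation of 0.07 mm, 63 patients are needed in each group"), d = 0.5/0.07 = 7.14 and n = 0.31, so 1 per group. The figure of 63 does not follow from them. That is a separate defect.
- With d = 0.5, n = 62.8, so 63. Then 63/0.85 = 74.1, so 75 per group.

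The 63 is therefore reproduced by a formula for individually randomized patients with design effect 1, at an inferred effect of 0.5 SD.

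**Step 2: which reading gives 75 per group?** 150/10 = 15 sets.
- Whole clusters: 75/10 = 7.5 clusters per arm, which is impossible. The nearest split is 8 against 7, or 80/70 patients.
- Permuted blocks of 5+5: 15 × 5 = 75 per arm, exactly as planned.

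**Step 3: predictability with fixed blocks of 10.** The last allocations in a block are forced once one arm has used its five places. On average 5/6 of an A place follows the last B, and 5/6 of a B place follows the last A. The expected forced tail is 5/6 + 5/6 = 10/6 = 1.67 per block (simulation: 1.67). Over 15 blocks this is 25 of 150, or 17%.

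**Step 4: literal clusters of 10, all with the same cup.** After the first envelope of each set, the other nine are determined: 15 × 9 = 135 of 150 (90%), at most.

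The documents give no ICC, so the values below are assumptions.
- Design effect: DE = 1 + (10 − 1) × ICC.
- Type I error of the unadjusted test: 2[1 − Φ(1.96/√DE)].
- Power: that of a t-test with 63/DE effective patients per group at 0.5 SD.

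| ICC | DE | Type I error | Effective n per group | Power |
|---|---|---|---|---|
| 0 | 1.00 | 5.0% | 63 | 80% |
| 0.01 | 1.09 | 6.0% | 57.8 | 76% |
| 0.05 | 1.45 | 10.4% | 43.4 | 63% |
| 0.10 | 1.90 | 15.5% | 33.2 | 52% |

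The normal approximation gives power about one point higher (77%, 64%, 53%).

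**Step 5: allowing for drop-out.** If 63 of 75 are analysed, the mean analysed set is 10 × 63/75 = 8.4. For ICC 0.01, 0.05 and 0.10, DE falls to 1.07, 1.37 and 1.74. Type I error is then 5.9%, 9.4% and 13.7%, and power by the normal approximation is 77%, 67% and 57%.

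**The case against.** The strongest reply is that this is one wrong word. The preceding sentence randomizes patients, there is a single department, the target is exactly balanced, and every analysis is at patient level. All of this fits blocks of ten mislabelled as clusters, and under blocks the design effect is 1. That argument stands, and it governs how large the point is.

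A reader might infer from the printed sentence that concealment is lost for nine of every ten patients. The documents do not support that as a fact. It would need sets that share one cup, staff who know where each set begins, and a first envelope opened before the other nine patients are enrolled. Patients are already scheduled for surgery at inclusion and envelopes are opened a week before it, so several may be enrolled before any opening. The article does not say who recruits.

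A reader might also infer that the t-test and the sample size are invalid. That too goes beyond the text. It requires literal clusters and an ICC above zero, and at an ICC of 0.01 the type I error is only about 6%. The power losses also rest on the inferred 0.5 SD effect. With the printed 0.5 mm and SD 0.07 mm, power at 63 per group stays near 100% at every ICC shown.

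On blocks, it is fair to say that a fixed block size is not in itself an error, and that the plan already has an independent planner, a computer-generated sequence and concealed envelopes. The 17% applies only if staff know the block size and follow the allocations. The plan does, however, print the number ten and leaves two people at one centre aware of the allocations.

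What the reply does not remove is the contradiction. The article does not leave the unit of randomization to a fuller document; it states one that conflicts with its own sample size and analysis.

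**Conclusion.** The point holds as a contradiction about the unit of randomization, and it needs correcting because the sentence, if followed, gives a design that the sample size and tests do not fit.

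- **Most likely case, permuted blocks of 10:** 63 and 75 per group and the t-test need no cluster correction. The remaining weakness is about 25 of 150 allocations deducible, on the condition that unblinded staff know the block size and keep track.
- **Less likely case, same-cup clusters:** up to 135 of 150 allocations would be foreseeable, as an upper bound. The patient-level test would be anti-conservative, with type I error of about 6% to 16% and power of about 76% down to 52%. These figures assume ICC 0.01 to 0.10, an inferred 0.5 SD effect and ten analysed patients per cluster, and are somewhat milder after drop-out.

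**What to change.** In the Design section, replace the words on cluster randomization per 10 patients with: *Patients are individually randomized 1:1 in permuted blocks of randomly varying size, with block sizes not disclosed to the surgeon or primary investigator.* Keep the statement that an independent planner generates the sequence by computer.

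If clusters were truly intended, define them, state an ICC with its basis, restate the power or sample size with the design effect, and use a cluster-adjusted analysis. For scale, at 0.5 SD with ten per cluster, an ICC of 0.05 would need 63 × 1.45 = 91.4, so 92 evaluable patients per group, and 92/0.85 = 108.2, so 109 enrolled per group.

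Opening envelopes nearer to surgery would shorten the time in which the cup is known beforehand. That is an optional preference; nothing in the document contradicts the one-week interval.

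The cost is one sentence and a regenerated list. With varying block sizes, the final groups may differ from 75/75 by a few patients.

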### Study population

The study will be conducted at the Department of Orthopaedic Surgery of the Martini Hospital, Groningen, the Netherlands. Patients to be included suffer from non-inflammatory degenerative joint disease of the hip and are scheduled for a primary unilateral total hip arthroplasty, and are aged under 70 years. Exclusion criteria are secondary osteoarthritis of the hip, (active) arthritis (e.g. rheumatic disease), peripheral neuropathy, history of CVA or cognitive impairment (e.g. dementia). Participation in the study is voluntary and informed consent is required. The inclusion period is planned from January 2012 to January 2014.

### Intervention

Both investigated groups will receive a reversed hybrid total hip arthroplasty. Gentamycine cement (Palacos®R + G, Heraeus) will be used for cup fixation, applying third-generation cementing techniques including vacuum mixing, pulsed lavage and pressurization. The same cementless 28-mm femoral component is used in both groups: a proximally plasma-sprayed porous coated titanium alloy (Ti6Al4V) stem (Mallory-Head®, Biomet) with a cobalt-chromium-molybdenum 28 mm femoral head.

One group will receive a cemented vitamin E-stabilized highly cross-linked polyethylene acetabular component (E1™ Muller cup, Exceed ABT Cemented Cup System, Biomet). The other group will receive a cemented conventional cross-linked polyethylene acetabular component without the adjunction of vitamin E (ArCom™ Muller cup, Exceed ABT Cemented Cup System, Biomet).

A posterolateral surgical approach in lateral decubitus position is used. Antibiotic prophylaxis with first-generation cephalosporin will be given preoperatively and during the first 24 hours intravenously.

### Follow-up

In this study the main outcome parameter is polyethylene wear (mm/y) 10 years postoperatively. Secondary outcome parameters are periacetabular bone mineral density, periprosthetic osteolysis, patient- and physician-reported outcome and implant survival (Table
1). Depending on the outcome parameters, measurements will take place preoperatively, 6 weeks, and 1, 3, 5, 7 and 10 years postoperatively.

**Table 1 T1:** Secondary outcome parameters

	
1.	polyethylene wear at 1, 3, 5 and 7 years postoperatively
2.	relative decrease/increase in acetabular bone mineral density (BMD) at 1 and 2 years postoperatively
3.	acetabular and proximal femoral osteolytic changes at 1, 3, 5, 7 and 10 years postoperatively
4.	patient-reported functional outcome (HOOS and SQUASH) at 6 weeks and at 1, 3, 5, 7 and 10 years postoperatively
5.	physician-reported functional outcome (Harris Hip Score) at 6 weeks and at 1, 3, 5 and 10 years postoperatively
6.	survival (number of revisions) determined at 5 and 10 years postoperatively

Other study parameters: gender, age, *BMI*, severity of arthrosis, complications, size and inclination of the cup, surgical time and intraoperative blood loss.

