#### Multivariate analysis

A GEE (Generalized Estimating Equation) analysis will be used to determine whether there is a difference on the primary and secondary outcome variables between the two groups over time, adjusted for relevant covariates. A p-value of < 0.05 is considered statistically significant.

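### Implant survival is defined as a count of revisions at two visits and reaches analysis only through a blanket GEE; a time-to-first-revision analysis suits it better

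*Protocol article*

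**What the plan says.** - **Measure.** Protocol article, Follow-up, Table 1 item 6: "survival (number of revisions) determined at 5 and 10 years postoperatively". The abstract mentions the later reading only: "Implant survival will be determined at 10 years postoperatively".
- **Hypothesis.** The Background expects "increased implant survival in polyethylene incorporated with vitamin E (secondary outcome parameters) in the long term". The Conclusion also names survival among the things the trial is designed to determine.
- **Univariate analysis.** A t-test covers wear at 10 years. The same test, or a non-parametric equivalent, covers "Differences in other outcome measures (osteolytic changes, bone mineral density, HOOS, Harris Hip score, SQUASH) between the two groups". Implant survival is not in that list.
- **Multivariate analysis.** A GEE, adjusted for relevant covariates, is to assess a "difference on the primary and secondary outcome variables between the two groups over time". Survival is a secondary outcome, so this sentence takes it in.
- **Expected loss.** The Sample size section says "Based on previous studies we expect a drop-out rate of 15" per cent and plans 75 patients per group. No revision rate, number of revisions or power for survival is given anywhere.

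**The concern.** Survival of an implant is a time-to-event outcome. Over ten years some patients will leave or die with the implant in place, and each contributes a known period without revision. A count at 5 and 10 years has no natural place for them: they stay in the denominator as if unrevised, or they drop out of it. Each choice gives a different survival figure, and if loss differs between arms the choice enters the comparison.

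The GEE is also a poor match. Revision is a one-way event and may be rare. If one arm has no revisions, the group effect on a ratio scale (odds, risk or rate ratio) has no finite estimate. If there are only a few, adjusting for covariates is unreliable. At stake is the estimate for a hypothesis the article states explicitly.

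**Working it through.** **Inputs.** From the article: 75 per group; 15% drop-out; readings at 5 and 10 years. The planned number follows from its own inputs: 63 / 0.85 = 74.1, rounded up to 75. The article gives no survival figure to reproduce. Assumed here: ten-year revision risk p of 2%, 3%, 5% or 10%, constant hazard, and loss spread evenly over ten years. A 25% loss is added as an assumed case for drop-out plus death.

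**Step 1: effect of loss on the count.** Take p = 5%.
- Hazard per year: λ = -ln(0.95)/10 = 0.00513.
- Mean risk up to a uniform loss time: 1 - 0.05/0.0513 = 0.0252.
- All randomised patients in the denominator, 15% loss: 0.85 × 0.05 + 0.15 × 0.0252 = 0.0463. Relative to 0.05 this is -7%.
- Patients lost unrevised removed from the denominator, observed revisions kept: 0.0463 / (1 - 0.15 × 0.9748) = 0.0542, or +8%.
- With 25% loss, the same steps give 0.0438 (-12%) and 0.0579 (+16%).

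In patients, the first bias at 15% loss is 75 × (0.0500 - 0.0463) = 0.28 per arm. Equal loss shifts both arms alike. With 10% loss in one arm and 20% in the other, the all-randomised figures are 0.0475 and 0.0450, so a true risk ratio of 1.00 appears as about 0.95.

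**Step 2: chance of an arm without revisions.** With equal risks and full follow-up of 75 per arm, P(at least one empty arm) = 1 - [1 - (1 - p)^75]². The five-year risk is 1 - (1 - p)^0.5.

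| Assumed 10-year risk | Expected revisions by 10 years, both arms | Empty arm by 5 years | Empty arm by 10 years |
|---|---|---|---|
| 2% | 3.0 | 72% | 39% |
| 3% | 4.5 | 54% | 19% |
| 5% | 7.5 | 27% | 4% |
| 10% | 15.0 | 4% | under 0.1% |

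Example for 2%: 0.98^75 = 0.220, and 1 - 0.780² = 0.39. If the vitamin E arm had half the hazard, the ten-year figures would be 59%, 39%, 16% and 2%. The ten-year column governs a single group effect across both visits; the five-year column governs a group effect at 5 years or a group-by-time term.

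**Step 3: what a time-to-event test could detect.** Power = Φ(|ln HR| × √(d/4) - 1.96), with d revisions.
- 5% versus 2.5%: d = 75 × 0.075 = 5.6, HR = 0.494, power about 13%.
- 10% versus 5%: d = 75 × 0.15 = 11.25, HR = 0.487, power about 23%.

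**The case against.** The strongest reply is that a journal article condenses a fuller plan. Its name for the outcome is implant survival, the words in brackets may only identify revision as the event, and censoring rules and competing events are commonly left to the full document. The GEE sentence is generic and never names survival. On this view the silence about Kaplan-Meier or log-rank methods is no finding.

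That last part stands: the missing names and censoring rules are not counted here. What remains is that the article does state a measure, a count at two visits, and does assign a model to all secondary outcomes. Those statements fit survival poorly.

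Other parts of the reply also stand, and they limit what a reader might infer:
- **That the GEE will often fail.** This rests on a revision rate the article does not give. It is plausible at assumed risks of 2% to 3%, holds at 5% mainly for the five-year reading, and is unlikely near 10%.
- **That a hip revised twice is counted twice, or that lost patients are treated as unrevised.** The text says neither. The handling is simply open.
- **That follow-up time is ignored and partial follow-up wasted.** Readings at two visits use time coarsely, a count keeps every observed revision, and a GEE can keep the five-year status of someone lost later.
- **That the loss bias is large.** At 15% loss and 5% risk it is about a quarter of a patient per arm. Sampling error is far larger: 4 revisions in 75 has an exact 95% interval of roughly 1.5% to 13%.

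Finally, no method would make this a well-powered comparison, as Step 3 shows.

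**Conclusion.** The point holds in a limited form. The article fixes implant survival as a revision count at 5 and 10 years, and the only stated comparison reaching it is a covariate-adjusted GEE. That combination does not use revision dates, time at risk, or censoring by death and drop-out.

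The bias from loss is modest, about -7% or +8% relative under 15% uniform loss and an assumed 5% risk, and matters for the comparison mainly if loss differs by arm. The chance that a GEE ratio has no finite estimate runs from 27% to 72% at 5 years and from 4% to 39% at 10 years for assumed ten-year risks of 5% down to 2%. These ranges rest on assumed revision rates, equal risks, constant hazard and 75 followed per arm.

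Even where the model can be fitted, 3 to 7.5 expected revisions at those risks are too few for reliable covariate adjustment. The matter concerns one secondary outcome. It does not touch the primary wear comparison or the sample size, but it should be put right because survival is a named hypothesis.

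**What to change.** 1. In Table 1 item 6, define the outcome as time from surgery to first revision, compared by randomised arm, with patients not revised censored at last contact.
2. In the Multivariate analysis section, exclude implant survival from the GEE.
3. Report cumulative incidence of revision at 5 and 10 years with 95% confidence intervals, treating death as a competing event, and compare arms with Gray's test. The alternative is Kaplan-Meier with a log-rank test, in which death is censored rather than treated as a competing event; if that is chosen, say so.
4. Present the result as an estimate, since few events are likely.

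**Cost.** A few sentences of wording, slightly more analysis work, and recording of the dates of revision, death and last contact, which the article does not say are collected. No extra patients or visits are needed. The change makes the analysis fit the outcome; it does not remedy the low power.
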